### Sample size

The sample size was calculated following recommendations for comparing two means in intervention studies (23). As the Fugl-Meyer Assessment (FMA) was the main outcome, change in this measure was selected as the primary criterion. Following previous research (24), the minimal difference in scores used to detect between-group differences in motor improvement was 4, assuming a standard deviation of 12. Using a two-tailed t-test for the difference between means with 80% power and a 5% level of significance, the sample size required was 70 participants, with 35 per group. Considering a dropout rate of 10%, the final required sample size was estimated at 76 participants, with 38 per group.

Given the specificity of the target population and the outpatient rehabilitation context, recruitment will be conducted in successive phases. The first recruitment phase, conducted in a single center, is expected to include approximately 24 eligible and recruitable participants, with 12 participants per group. Subsequent phases will include additional outpatient neurological rehabilitation centers in the Community of Madrid until the total required sample size of 76 participants is reached. Based on the projected recruitment capacity across participating centers, completion of recruitment is expected within approximately 1 year.

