### Randomization and allocation

The study follows a randomized waitlist-controlled design:Experimental group: standard rehabilitation care plus music-based intervention during the first intervention phase.Control/waitlist group: standard rehabilitation care during the first intervention phase, followed by music-based intervention after completion of the experimental group intervention.

Random allocation will take place after obtaining informed consent.

The selection, randomization, and follow-up process will be represented in a flow diagram (Figure 1), consistent with recommendations for waitlist-controlled trials. Randomization will be generated by a member of the research team using simple randomization software. If recruitment is extended to additional centers, randomization will be monitored across centers to maintain balance between groups within each recruitment phase. Group allocation will be concealed until the point of assignment to ensure masking of the sequence.

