Musical parameters, including tempo, rhythmic complexity, movement amplitude, instrument type, and level of facilitator cueing, will be adapted according to participants’ motor capacity, fatigue, comprehension, and emotional response. Tasks will begin at a level that allows successful participation and will progress by increasing rhythmic complexity, tempo, task duration, bilateral involvement, range of movement, memory load, or degree of independence. Task difficulty will be reduced if participants show excessive fatigue, frustration, loss of postural control, inability to follow instructions, or emotional discomfort. Treatment fidelity will be supported through facilitator training, use of the standardized session protocol, and completion of a session checklist documenting attendance, activities delivered, adaptations made, participant engagement, adverse events, and deviations from the protocol.

Session checklists will be reviewed periodically by the research team to monitor adherence to the protocol and identify deviations requiring corrective action.

The intervention consists of a 10-session structured program delivered twice per week over 5 weeks, including 6 individual sessions and 4 group-based sessions.Individual sessions (30–40 min): Focused on evaluation and individualized work on motor engagement, rhythmic participation, and emotional regulation.Group sessions (45 min): Conducted collectively with all participants, focused on social interaction, motor coordination, and emotional support.

These group-based and receptive components are informed by music therapy and music-based rehabilitation approaches commonly used to support emotional regulation, social interaction, and quality of life in rehabilitation populations. Group singing, shared rhythmic activities, and guided listening are consistent with rehabilitation-oriented music-based frameworks that emphasize emotional expression, social engagement, and patient-centered rehabilitation (6, 7).

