### Statistical analysis

Statistical analysis will be carried out using Jamovi (version 2.7.26). Qualitative variables will be described using frequencies (N) and percentages (%). Number of observations (N), mean, median, standard deviation, minimum, and maximum will be used to describe quantitative variables. Missing data will be reported descriptively, including the extent and pattern of missingness across time points.

Baseline demographic and clinical characteristics will be described. The outcome measures will be calculated according to their guidelines. Scores will be reported at all time points (baseline, 5 weeks, 10 weeks, and 3-month follow-up). A linear mixed-effects model (MLM) will be carried out to estimate the main effect of the intervention on the primary outcome, motor function assessed using the FMA. Additional models will be conducted to estimate the secondary motor outcome, upper-limb motor function assessed using the ARAT. Exploratory models will be conducted for cognitive flexibility (WCST), self-perceived executive functioning (BRIEF-A), and stroke-specific quality of life (SS-QOL). These exploratory analyses will be interpreted cautiously and will be used to inform future research rather than to establish definitive efficacy in these domains. The model will include time, group, and the interaction between group and time as fixed effects. Time after stroke will be included as a covariate to account for variability related to recovery stage. A random intercept will be specified to account for repeated measures. Model parameters will be estimated using restricted maximum likelihood (REML), which allows analysis without assuming sphericity. Degrees of freedom will be computed using the Satterthwaite method.

To explore agreement between participant and family member reports on the BRIEF-A executive function questionnaire, additional analyses will be carried out using intraclass correlation coefficients (ICC). Bland–Altman plots will be used to assess systematic bias and limits of agreement between informants.

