### Limitations

This randomized waitlist-controlled intervention study presents several inherent limitations. First, outcome assessors will not be blinded, which may introduce measurement bias despite the use of standardized procedures and trained personnel. Second, although this study begins in a single outpatient rehabilitation center, recruitment is planned to proceed in successive phases across additional centers in the Community of Madrid. This phased recruitment strategy may improve feasibility but may also introduce some variability between centers, which will be addressed through standardized intervention procedures, assessor training, fidelity monitoring, and statistical adjustment when appropriate. Third, the relatively short duration of the intervention may reduce the magnitude of observable effects.

In addition, although the sample size was determined through an *a priori* calculation, potential dropout, variability in clinical profiles, and differences in recruitment flow across centers may still affect statistical power and study implementation. These factors should be considered when interpreting the findings. Future studies may explore longer or more intensive protocols and broader multicenter recruitment strategies to further evaluate the impact of integrative music-based interventions.

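### The primary model leaves out correlation from shared group sessions, which makes the week-5 standard error too small, and the centre/phase adjustment is left to discretion

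*Protocol article*

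**What the plan says.** **Model.** The Statistical analysis section gives fixed effects for time, group and group by time, one covariate (time since stroke), REML estimation and Satterthwaite degrees of freedom. The only random term is this: "A random intercept will be specified to account for repeated measures". There is no term for session group, centre or recruitment phase.

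**Delivery.** The Music-based intervention section and Table 1 give six individual and four group sessions. The group sessions are "Conducted collectively with all participants, focused on social interaction, motor coordination, and emotional support". The waitlist arm starts the programme only after the experimental arm has finished it (Study design).

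**Centres.** The trial starts in one centre, with about 12 participants per arm, and extends to others until 76 are enrolled. Standard care follows each centre's own practice (Standard rehabilitation care). Randomization and allocation specifies simple randomization and adds that, if centres are added, "randomization will be monitored across centers to maintain balance between groups within each recruitment phase". Limitations says that between-centre variability will be handled by measures that end with "fidelity monitoring, and statistical adjustment when appropriate". The form of that adjustment and the condition for using it are not given.

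**The concern.** There are two separate issues, and they act in different directions.

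**Shared sessions.** People who drum, sing and improvise together under the same facilitation may respond alike. This correlation arises after baseline, so it affects change from baseline and does not cancel within a person. Up to week 5 it exists in one arm only. A model that treats participants as independent then overstates the information in the experimental arm, and the test rejects too often. From week 5 to week 10 the waitlist arm is clustered in the same way.

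**Centre and phase.** Because standard care differs by centre, so may change over five weeks. If balance is enforced within phase, leaving the factor out of the model wastes precision. If the decision to adjust stays open, an adjusted and an unadjusted primary result are both compatible with the text.

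**Working it through.** **The plan's own figure.** Sample size takes these inputs: "the minimal difference in scores used to detect between-group differences in motor improvement was 4, assuming a standard deviation of 12". The method is "Using a two-tailed t-test for the difference between means with 80% power and a 5% level of significance", and the stated result is "the sample size required was 70 participants, with 35 per group". Recomputed by the normal formula, n per arm = 2 × (1.960 + 0.842)² × 12² / 4² = 141.3, so 142 (143 with the t distribution). That is about 284 in total, not 70. The dropout step reads "Considering a dropout rate of 10%, the final required sample size was estimated at 76 participants, with 38 per group", while 70 / 0.9 = 77.8. The shortfall is a separate and larger problem. It matters here only because the calculation has no clustering allowance, and any such allowance would come on top.

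**Shared sessions.** Inputs: clustering in the experimental arm only (from the delivery schedule), group size m and ICC of the change score ρ. Both m and ρ are assumed. The upper value m = 12 is the expected phase-1 experimental arm.

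- Design effect in the experimental arm: DE = 1 + (m − 1)ρ
- Variance factor for the difference with equal arms: V = (1 + DE) / 2
- True SE / model SE = √V; shortfall of the model SE = 1 − 1/√V
- True two-sided alpha = 2 × [1 − Φ(1.96 / √V)]

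Example with m = 12 and ρ = 0.05: DE = 1 + 11 × 0.05 = 1.55; V = 1.275; √V = 1.129; shortfall = 11.4%; alpha = 2 × [1 − Φ(1.736)] = 8.3%.

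| m | ρ | √V | Model SE too small by | True alpha |
|---|---|---|---|---|
| 4 | 0.01 | 1.007 | 0.7% | 5.2% |
| 4 | 0.10 | 1.072 | 6.7% | 6.8% |
| 6 | 0.05 | 1.061 | 5.7% | 6.5% |
| 12 | 0.01 | 1.027 | 2.6% | 5.6% |
| 12 | 0.02 | 1.054 | 5.1% | 6.3% |
| 12 | 0.05 | 1.129 | 11.4% | 8.3% |
| 12 | 0.10 | 1.245 | 19.7% | 11.5% |

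A null simulation checked this. It used 20,000 runs, 76 participants, four assumed centres of 24, 18, 18 and 16, and one session group per centre. The test was a t-test on change scores, which equals the random-intercept group-by-time contrast when there are two time points and no covariate. For ρ of 0.02, 0.05 and 0.10, alpha was 5.9%, 7.8% and 10.4%. At ρ = 0.05 the empirical SE was 0.254 against a model SE of 0.228. These values sit slightly below the m = 12 rows because the assumed groups are smaller (12, 9, 9 and 8).

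**Centre.** The same simulation was run with a centre effect on change and no session-group effect.

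| Centre ICC | Allocation | Empirical SE | Model SE | Alpha |
|---|---|---|---|---|
| 0.05 | balanced within centre | 0.221 | 0.227 | 4.3% |
| 0.10 | balanced within centre | 0.217 | 0.226 | 4.2% |
| 0.05 | simple | 0.231 | 0.229 | 5.0% |
| 0.10 | simple | 0.228 | 0.227 | 5.1% |

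Omitting centre is therefore slightly conservative when arms are balanced within centre, and neutral under simple randomization. A centre effect on level alone drops out of the within-person contrast.

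**The case against.** - **The size is assumed.** No ICC or session-group size is documented, six of the ten sessions are individual and tailored, and the outcome is a motor score. An ICC of 0.10 has no support in the text, and with groups of four alpha stays at or below 6.8%. This stands, and the result should be read as a range. The direction does not depend on it: any positive ICC makes the stated model anti-conservative.
- **Centre.** A reader might infer that leaving out centre also makes the standard error too small, or that randomization is stratified by centre. The documents support neither. The simulation shows a neutral or conservative effect, and the text promises monitored balance within phase under simple randomization.
- **Cohorts.** A reader might infer that one facilitator treats the whole experimental arm of a phase as a single group. The protocol does not say so. It refers to several facilitators trained at each centre, and later phases may span several centres.
- **Detail for an analysis plan.** An unseen plan could fix the adjustment rule in advance, and the statistician works with coded groups, so it cannot be said that the choice will follow sight of the data. That is fair. However, the article states a definite primary model and, elsewhere, a conditional adjustment that this model does not contain, and the two need reconciling. Coding the groups does not prevent a choice between two p-values.
- **The remedy leaves the primary test unchanged for clustering.** This is true. With 38 in the experimental arm and groups of 12 there would be about three groups (38 / 12 = 3.2), too few for a stable variance estimate in the primary model.

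**Conclusion.** The point holds in two parts. First, the stated model omits session-group correlation that, before week 5, can exist only in the experimental arm. If that correlation is positive, the standard error of the week-5 contrast is too small. For m from 4 to 12 and ICC from 0.01 to 0.10 the shortfall is about 1% to 20%, with true alpha of about 5.2% to 11.5%; at m = 12 and ICC 0.05 it is about 11% and 8.3%. These figures rest on assumed inputs, equal arms and a change-score approximation to the mixed model.

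Second, centre/phase adjustment is neither in the model nor governed by a rule. The consequence is possible loss of precision and an open choice of primary estimate, not an inflated error rate from the omission itself. Both parts warrant a change before recruitment starts; neither invalidates the design.

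**What to change.** 1. Add centre (or recruitment phase) by visit as a fixed effect in the longitudinal primary model. A centre main effect alone would not help, because it cancels from the within-person contrast. Delete the conditional wording in Limitations and refer to this term instead.
2. Record a session-group identifier for every participant. The session checklist already documents attendance, so this is one extra field.
3. Prespecify a partially nested sensitivity analysis: a random session-group effect in the intervention condition only, with small-sample degrees of freedom. Because groups will be few, repeat it over a range of fixed ICCs.
4. State in advance that the primary conclusion will be tempered if it does not hold in that analysis.

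Cost: a few degrees of freedom, one recorded variable and a possibly slightly wider interval. The session-group variance will be imprecise, which is why it belongs in a sensitivity analysis. According to Study status, recruitment has not begun, so no collected data are affected.

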### Follow-up

A follow-up interview will be scheduled 3 months after completion of the intervention to explore the maintenance of potential effects, the continued use of music-based strategies at home, and participants’ perceived acceptability, usefulness, and relevance of the intervention in their daily lives.

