### Dropout and missing data management

Given the longitudinal design of the study, particular attention will be paid to participant retention and data completeness. Protocol completion will be defined as participation in at least 80% of the scheduled sessions (i.e., at least 8 of 10 sessions).

The primary analysis will follow the intention-to-treat (ITT) principle, including all randomized participants with available outcome data in the analysis set. Linear mixed-effects models will use all available repeated-measures data under the missing-at-random assumption, without formal imputation. The extent and patterns of missing data will be reported descriptively.

An additional per-protocol analysis will be conducted, including only participants who meet the predefined completion threshold.

Dropout rates, reasons for withdrawal, and patterns of missing data will be reported descriptively to support transparent interpretation of the study findings.

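### The protocol credits REML with avoiding the sphericity assumption, but the random-intercept model it names imposes compound symmetry, so visit-specific standard errors can be wrong

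*Protocol article*

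**What the plan says.** The Statistical analysis section of the protocol article sets out one linear mixed model for the primary outcome (FMA motor score), with further models for the other outcomes. On fixed effects: "The model will include time, group, and the interaction between group and time as fixed effects". Time since stroke is added as a covariate. On the repeated measures: "A random intercept will be specified to account for repeated measures". On estimation: "Model parameters will be estimated using restricted maximum likelihood (REML), which allows analysis without assuming sphericity". On inference: "Degrees of freedom will be computed using the Satterthwaite method". No random slope, residual correlation structure, visit-specific variance or robust standard error is named.

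Scores are reported at baseline, week 5, week 10 and a 3-month follow-up. The Follow-up section dates the last visit from the end of treatment: "A follow-up interview will be scheduled 3 months after completion of the intervention". The section on dropout and missing data adds: "Linear mixed-effects models will use all available repeated-measures data under the missing-at-random assumption, without formal imputation".

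**The concern.** Sphericity concerns the covariance of the repeated measurements: all differences between pairs of visits have the same variance. Whether a model assumes it depends on its covariance structure, not on whether its parameters are estimated by REML or by another method. A random intercept with independent, equal-variance residuals gives every visit the same variance and every pair of visits the same correlation. That is compound symmetry, a special case of sphericity. The text therefore attributes to the analysis a freedom that the named model lacks. Satterthwaite degrees of freedom do not restore it, because they are computed from whatever covariance structure has been fitted.

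The design gives reason to doubt equal correlation. The visits fall at weeks 0, 5 and 10 and then about three months after treatment, and measurements further apart usually correlate less. The Inclusion criteria admit both late subacute (3 to 6 months) and chronic patients, who may recover at different rates. Time since stroke entered as a covariate shifts the level of a participant's scores and does not absorb differing slopes.

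At stake are the standard errors of the group differences in change. A single pooled residual variance serves every visit, so a contrast between close visits can get too large a standard error and one between distant visits too small a one.

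**Working it through.** The protocol gives no between-visit correlation and no figure on this point, so there is nothing of its own to reproduce. The check asks what the named model does under several assumed true covariances.

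**Inputs from the protocol.** k = 4 visits; n = 35 per group (Sample size section); random intercept; REML; two-sided 5% level.

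**Assumptions.** Independent, equal-variance residuals; time as a categorical factor; complete data; contrasts of each visit against baseline. Three months is taken as about 13 weeks, which puts follow-up at week 18 (counted from week 5) or week 23 (counted from week 10).

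**Step 1: residual variance under the model.** With complete balanced data, the random-intercept REML residual variance targets

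s² = (mean visit variance) − (mean covariance over all pairs of visits).

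**Step 2: model and true variance of a group difference in change.**

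- Model: 2s² × 2/n, identical for every visit.
- True: Var(Yj − Y0) × 2/n, which may differ by visit.
- Ratio of model to true standard error = √[2s² / Var(Yj − Y0)]; n cancels. With equal visit variances the SD cancels too.

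**Step 3: type I error.** About 2[1 − Φ(1.97 × ratio)], where 1.97 is the t critical value on (70 − 2) × 3 = 204 degrees of freedom.

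**Worked example: AR(1) by visit order, correlation 0.9.** The six pairwise correlations are 0.9 (three pairs), 0.81 (two) and 0.729 (one). Their mean is (2.7 + 1.62 + 0.729)/6 = 0.8415, so s² = 0.1585σ² and 2s² = 0.317σ².

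- Week 5: true change variance 2(1 − 0.9)σ² = 0.20σ²; ratio √(0.317/0.20) = 1.26; type I error 1.3%.
- Week 10: 2(1 − 0.81)σ² = 0.38σ²; ratio √(0.317/0.38) = 0.91; type I error 7.2%.
- Follow-up: 2(1 − 0.729)σ² = 0.542σ²; ratio √(0.317/0.542) = 0.76; type I error 13.2%.

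A simulation of this case with a REML random-intercept fit (400 trials) rejected in 1.8%, 7.5% and 14.3% of null trials.

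**Range over assumed structures.** Each cell gives the ratio of model to true standard error, with approximate type I error in brackets.

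| Assumed true covariance | Week 5 | Week 10 | Follow-up |
|---|---|---|---|
| Compound symmetry, correlation 0.8 | 1.00 (5%) | 1.00 (5%) | 1.00 (5%) |
| AR(1) by visit order, 0.9 | 1.26 (1.3%) | 0.91 (7.2%) | 0.76 (13.2%) |
| AR(1) by visit order, 0.8 | 1.23 (1.6%) | 0.91 (7.1%) | 0.79 (12.1%) |
| Continuous-time AR, 0.9 per 5 weeks, follow-up week 18 | 1.35 (0.8%) | 0.98 (5.3%) | 0.76 (13.3%) |
| Same, follow-up week 23 | 1.49 (0.3%) | 1.08 (3.3%) | 0.76 (13.4%) |
| Random slope, SD 0.2 per week, follow-up week 18 | 1.06 (3.6%) | 1.01 (4.6%) | 0.89 (7.8%) |
| Same, follow-up week 23 | 1.11 (2.8%) | 1.06 (3.7%) | 0.85 (9.2%) |
| SDs 10, 11, 12, 14 with correlation 0.8 | 1.16 (2.2%) | 1.08 (3.3%) | 0.92 (7.0%) |

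The random-slope rows use an intercept variance of 130 and a residual variance of 14.

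**The case against.** The strongest reply is that the protocol never says the residuals are independent, and that a residual covariance structure is the kind of detail an analysis plan supplies. On that view only a loosely worded clause is left, perhaps meant to say that a mixed model is used instead of repeated-measures ANOVA. It is true that an unseen plan may name another structure. But this is not merely a missing detail: the protocol names a random intercept as its means of handling the repeated measures and then states a property that REML does not confer. A plan that followed the protocol would carry the error forward, and one that departed from it would contradict the protocol.

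The reply is right on three further points.

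- The harm is conditional. If compound symmetry is true, the standard errors are right. A treatment switch in one arm does not by itself make correlations unequal, because it acts first on the means, which the group-by-time term models.
- A reader might infer that the week-5 comparison carries an inflated false-positive risk. None of the cases examined supports that; at week 5 the error is conservative. The inflation is largest at follow-up, which the protocol treats as exploring maintenance and which comes after both groups have had the programme.
- A reader might turn the ratios into power figures by taking 12 as the SD at one visit. The Sample size section does not support that reading: "the minimal difference in scores used to detect between-group differences in motor improvement was 4, assuming a standard deviation of 12". The SD is attached to improvement, so no absolute power figure is given here.

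**Conclusion.** The concern holds in a limited form. The statement about REML and sphericity is wrong for the model as described, and this needs no assumption beyond the default residuals that go with a random intercept. The effect on inference is a risk, not a demonstrated fault. Relative to the true standard error, the model's is exact under compound symmetry. In the non-spherical structures examined it is about 1.06 to 1.5 times the true value at week 5, costing power, and about 0.76 to 0.92 times at follow-up, where a nominal 5% test has about 7% to 13% type I error. Week 10 lies between, at 0.91 to 1.08. These ranges rest on assumed covariances, complete data, categorical time and visit-versus-baseline contrasts. The protocol fixes none of the covariances and names no visit-specific contrast. They show direction and plausible size and do not predict this trial's results. The error should be corrected before the analysis is fixed, but it does not undermine the randomised comparison itself.

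**What to change.** Delete the clause about sphericity. For every model that uses all four visits, replace the random-intercept-only structure with an unstructured within-participant covariance, fitted by REML, with Satterthwaite or Kenward-Roger degrees of freedom. If the chosen jamovi module cannot fit this, name another package.

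An unstructured 4 × 4 covariance has 4 variances and 6 covariances, 10 parameters against 2 for the random-intercept model. Eight more should be estimable with about 70 participants. Otherwise the cost is a change of wording and possibly of software. The Study status section says recruitment has not begun, so the change can be made before any data exist.

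A model restricted to baseline and week 5 would also avoid the problem for that one contrast. It is optional: which visit carries the primary test is a separate question, and curing this error does not depend on it.
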